**Participant Timeline:**

|  | **Study Period** | | | | | |
| --- | --- | --- | --- | --- | --- | --- |
|  | **Enrolment** | **Allocation** | **Post Allocation** | | | |
| **Time points** | **Screening** | **Baseline** | **15^th^ Day** | **30^th^ Day** | **60^th^ Day** | **90^th^ Day**  **(Close out)** |
| **Enrolment:** | | | | | | |
| Information and Informed consent |  |  |  |  |  |  |
| Eligibility evaluation |  |  |  |  |  |  |
| Allocation |  |  |  |  |  |  |
| Intervention: | | | | | | |
| Issue of Trial drug and Yoga Training to Group A |  |  |  |  |  |  |
| Training to practice ‘WHO Rehabilitation Self-Management after COVID-19’ to Group B |  |  | If required | If required | If required |  |
| Medical history and Demographic profile |  |  |  |  |  |  |
| Clinical examination |  |  |  |  |  |  |
| Prakriti (Constitution of body and mind) assessment |  |  |  |  |  |  |
| Assessment of Respiratory function, Fatigue, Sleep, Anxiety and Depression |  |  |  |  |  |  |
| Assessment of Quality of Life (COV19-QoL scale) |  |  |  |  |  |  |
| Laboratory and Radiological Investigations |  |  |  |  |  |  |
| Drug compliance |  |  |  |  |  |  |
| Rescue medication |  |  |  |  |  |  |
| Adverse events |  |  |  |  |  |  |

**Sample size:** The sample size for the study is calculated assuming improvement in 6-minutes walk test by 40 meter in Group I and a change of 10 meter in Group II with a standard deviation of 50 meter based on the results of the previous studies, with 95% Confidence Level (α = 0.05) and 80% power and expecting a dropout rate of 20%. The number of participants to be enrolled in the study should be approximately 55 in each group. Hence, a total of 110 participants will be enrolled in the trial at each study site.

**Recruitment:** The eligible participants will be screened from the patients with post COVID complaints visiting the Out-Patient Department of Government Medical College and Hospital, Nagpur and Datta Meghe Institute of Medical Sciences (Deemed as University),Wardha, Maharashtra, India.

**Randomization:** Statistical package for Social Sciences (SPSS) version 15.0 is used to generate the random number sequences. The participants will be randomized to two study groups in the ratio of 1:1.

**Allocation concealment:** The allocation concealment will be implemented through opaque, sealed envelopes. The allocation sequence will be generated by a statistician, who is not involved with the enrolment process.

**Blinding:** The study is open-label design. However, the outcome assessor will be kept blinded regarding the study group allocation of the participants.

**Data collection methods:** After informing the participants about the research study as per Patient Information Sheet, written consent (in triplicate) will be taken from the participants before screening them. After screening the participants, the eligible participants will be included in the study and data will be collected in a case record form. The data will be subsequently recorded in an e-format for statistical analysis and record.

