**Dissemination:** The Principle investigators at individual study centers will not report the data collected from their centers alone. All the presentations and publications will protect the integrity of the major objective(s) of the study. Data that break the blind will not be presented prior to the release of mainline results. Recommendations as to the timing of presentation of such endpoint data and the meetings at which they might be presented will be given by the CCRAS Headquarters.

**Appendices:** Informed Consent Form and Patient Information Sheet.

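### The sample size calculation gives 110 participants for the study, but the protocol assigns 110 to each of two sites, so the stated 80% power does not describe a pooled trial of 220

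*Protocol*

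**What the plan says.** The Sample size paragraph of the protocol rests on the 6-minute walk test, "assuming improvement in 6-minutes walk test by 40 meter in Group I and a change of 10 meter in Group II". Its other inputs are an SD of 50 m taken from earlier studies, α = 0.05, 80% power and 20% dropout. It concludes: "The number of participants to be enrolled in the study should be approximately 55 in each group". The scope of that sentence is the study. The sentence that follows is offered as its consequence and has a different scope: "Hence, a total of 110 participants will be enrolled in the trial at each study site".

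Study Setting names two hospitals. Study Design describes one multi-centre, two-arm, parallel-group trial with 1:1 allocation and calls it exploratory. Statistical methods gives a single between-group comparison and does not mention site. Dissemination says: "The Principle investigators at individual study centers will not report the data collected from their centers alone". No section prints an overall total.

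**The concern.** Two groups of 55 make 110 for the study. Assigning 110 to each of two sites makes 220, and the paragraph gives no step that leads from one to the other: no site-level objective, no inflation for site and no allowance for further endpoints.

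Two things depend on the answer. The first is the number of people exposed. Each participant has HRCT of the chest at baseline and day 90 and follows a 90-day assigned programme, and the written justification covers 110 people, not 220. The second is what the trial is designed to detect. If 220 is deliberate and the data are pooled, the design is sensitive to a clearly smaller difference than the 30 m on which it is justified, and the protocol does not say so. The optional interim analysis also depends on the total, because Data Monitoring ties it to 25% of participants completing: 0.25 × 110 = 27.5, so 28 people, against 0.25 × 220 = 55.

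**Working it through.** **Inputs (Protocol, Sample size).** Difference 40 − 10 = 30 m; SD 50 m, so the standardised difference is 30/50 = 0.60; α = 0.05; power 80%; dropout 20%. Allocation is 1:1 (Study Design) and there are two sites (Study Setting). Sidedness is not stated. Two-sided is assumed because it reproduces the protocol's figure; a one-sided test gives 35 evaluable and 44 enrolled per group, which does not.

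**Step 1: reproduce the stated figure.**

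n per group = 2 × (1.96 + 0.8416)² × (50/30)² = 43.6, rounded up to 44 evaluable.

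With dropout: 44 / 0.80 = 55 enrolled per group.

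Both groups: 2 × 55 = 110.

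This matches the stated 55 exactly, so the listed inputs account for the whole figure.

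**Step 2: size implied by the per-site sentence.**

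2 sites × 110 = 220 enrolled, 110 per group. After 20% dropout: 110 × 0.80 = 88 evaluable per group, 176 in all.

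**Step 3: power for 30 m, pooled, 6-minute walk only, two-sided 5%.**

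Power ≈ Φ(30 / (50 × √(2/n)) − 1.96).

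- n = 44: 30/10.66 = 2.81; Φ(0.85) = 80.4%.
- n = 88: 30/7.54 = 3.98; Φ(2.02) = 97.8%.

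**Step 4: difference detectable with 80% power.**

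Difference = (1.96 + 0.8416) × 50 × √(2/n).

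- n = 44: 29.9 m.
- n = 88: 21.1 m.

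| Enrolled in total | Evaluable per group | Power for 30 m, normal approximation (t-test) | Detectable at 80% power, normal approximation (t-test) |
|---|---|---|---|
| 110 | 44 | 80.4% (79.5%) | 29.9 m (30.2 m) |
| 220, pooled | 88 | 97.8% (97.7%) | 21.1 m (21.2 m) |

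**Step 5: which trial the 80% fits.** It fits a trial of 110 in total, or one site of 110 analysed alone. It does not fit a pooled trial of 220.

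**The case against.** The strongest reply is that each site was meant to be powered on its own. That is the one reading under which 110 per site and 80% power agree, and the protocol does not rule it out. The reporting rule in Dissemination limits what site investigators may publish and does not say how the sponsor will analyse the data. Statistical methods is silent on site either way. This much stands: pooling is an inference. Still, nothing in the protocol states a site-level aim or analysis, and a trial powered by site would also need its overall total and pooled power stated. The paragraph needs correcting on either reading.

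A second reply is that 220 is not hidden, since the only explicit enrolment commitment is per site and there are two sites. That is fair. What is missing is the printed total and its justification.

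A third concerns the scope of the power figures. Outcomes lists three primary measures, and the figures above cover one of them at an undivided 5%. If α were split equally over three (an assumption; the protocol gives no such rule), t-test power for 30 m would be 94.0% with 88 per group and 64.6% with 44. So the statement that 220 is twice the number required holds only for the single-endpoint calculation that the protocol presents.

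Three stronger readings are tempting and are not supported. A reader might infer an arithmetic error, but 44, 55 and 110 are each correct; only the scope changes. A reader might infer that the trial's validity is at risk, but a larger pooled trial has more power than stated, and neither the effect estimate nor the type I error is affected. What a null result excludes will come from the confidence interval obtained, not from this paragraph. Finally, a reader might suppose that the extra participants were meant to cover multiplicity or the analysis of everyone randomised; the protocol says neither.

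**Conclusion.** The point holds as an internal inconsistency that should be fixed. The calculation supports 110 participants for the study, while the enrolment sentence implies 220, a twofold gap with no explanation. If the data are pooled, as the design, the single between-group comparison and the reporting rule suggest, 220 gives about 98% power for 30 m, or 80% power for about 21 m, in place of the stated 80% for 30 m.

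This rests on a two-sided 5% test, the 6-minute walk as the only endpoint, the protocol's own SD and dropout rate, and pooling over two sites. The consequence is up to 110 participants without a stated justification and a design sensitivity that is not disclosed.

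**What to change.** State one overall total in the Sample size paragraph, with the power that matches it.

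- **If 220 is intended:** write 220 in total (110 per group, about 176 evaluable after 20% dropout), with about 98% power for a 30 m difference, or 80% power for about 21 m, on the 6-minute walk at two-sided 5%, analysed pooled. Add the sponsor's actual reason for this size. If the intent was to power each site separately, say so, and describe both the site-level analysis and the pooled one.
- **If 110 in total is intended:** remove the words that apply the figure to each site.

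No rationale that the protocol does not contain, such as multiplicity control, should be supplied after the fact.

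**Cost.** Confirming 220 takes one rewritten paragraph and no additional participants. Moving to 110 halves the enrolment in a protocol that both sites' ethics committees have approved. It is therefore an amendment, to be reported with its reason to the sponsor and the ethics committees as Protocol Amendments requires.

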**Study Setting**

- Two Academic Hospitals situated in Maharashtra, India viz. Government Medical College and Hospital, Nagpur and Datta Meghe Institute of Medical Sciences (Deemed as University),Wardha

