**Data management:**

**Statistical methods:**

The categorical variables in the study data will be summarized as number (percentage) and compared using chi-square test. The continuous data having normal distribution will be represented as mean (SD), and data not following normal distribution as median (min-max). Parametric data will be analyzed by paired t-test and independent sample t-test for within and between group analysis respectively whereas non-parametric data will be calculated by Wilcoxon signed rank test and Mann-Whitney test for within and between group analysis respectively. All the data analysis will be done using the STATA software version 16.1.

**Data Monitoring:** The study will be monitored by Data and Safety Monitoring Board (DSMB). An Interim analysis, if required can be done when at least 25% participants have completed their trial period.

**Ethics Approval:** The study protocol has been approved by the institutional Ethics committees of both the study sites viz., Government Medical College, Nagpur, India and Datta Meghe Institute of Medical Sciences, Wardha, India on 3^rd^ February 2021 and 24^th^ February 2021 (vide EC-CT-2019-0129 and EC/Pharmac/GMC/NGP/2309) respectively. The study will be conducted in accordance with the principles of Declaration of Helsinki and the ICMR’s National Ethical Guidelines for Biomedical and Health Research on Human Participants (2017).

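### Randomisation over two hospitals is stated only as 1:1 random numbers, with no site stratification, blocking or site term: a cheap, minor gain in precision is left unused

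*Protocol*

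**What the plan says.** The Study Setting section names two hospitals: "Two Academic Hospitals situated in Maharashtra, India". The Sample size paragraph gives "The number of participants to be enrolled in the study should be approximately 55 in each group" and continues: "Hence, a total of 110 participants will be enrolled in the trial at each study site". That makes 220 over the two sites, with about 55 per group at each.

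The Randomization paragraph reads "Statistical package for Social Sciences (SPSS) version 15.0 is used to generate the random number sequences", followed by "The participants will be randomized to two study groups in the ratio of 1:1". On concealment: "The allocation concealment will be implemented through opaque, sealed envelopes"; a statistician outside the enrolment process makes the sequence. The protocol does not mention blocks, strata, a separate list per site or site-specific envelope sets.

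The Statistical methods section assigns the between-group comparison to an independent-sample t-test, or to a Mann-Whitney test for non-normal data. Neither is given a site term. The Data Monitoring paragraph adds an optional early look: "An Interim analysis, if required can be done when at least 25% participants have completed their trial period".

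**The concern.** The size is set by site, but nothing in the stated allocation method holds the arms near 1:1 within a site. The two hospitals may differ in how they deliver the yoga and self-management training and in how they conduct the 6-minute walk and lung function tests. If mean change differs between sites and the arms split unevenly within a site by chance, part of the site difference enters the treatment contrast as noise. The planned test does not remove it.

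Precision is what is at stake. The allocation half of the remedy has to be in place before the first envelope is opened, because the list cannot be restricted afterwards. The analysis half can still be added later.

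**Working it through.** **Inputs.** From the Sample size paragraph: improvement of 40 m against 10 m (difference 30 m), SD 50 m, α = 0.05 (taken as two-sided), power 80%, dropout 20%, about 55 per group, 110 per site. Two sites. The between-site difference D in mean walk-test change is not in the protocol, so it is assumed here at 0, 20 and 40 m.

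**1. The plan's own figure.** n = 2(1.960 + 0.842)² × 50² / 30² = 43.6, so 44 per group. Dropout: 44 / 0.8 = 55. The stated 55 per group is reproduced. Normal-approximation power at 44 evaluable per group is 80.4%.

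**2. Split at one site if allocation is unrestricted.** The number in one arm is Binomial(110, 0.5), with SD √(110 × 0.25) = 5.2.
- 95% range: 45 to 65.
- Exactly 55:55: 7.6%.
- At least one of the two sites at 50:60 or worse: per site 0.391, so 1 − (1 − 0.391)² = 0.63.
- At least one site at 48:62 or worse: per site 0.215, so 1 − (1 − 0.215)² = 0.38.
- At 25% of participants (220 × 0.25 = 55, about 27 per site): 95% range 8 to 19.

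A single list balanced 110:110 overall but not by site would still give 48 to 62 at a site (hypergeometric).

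**3. Cost of unequal arms alone, at single-site size.** SE = 50√(1/n₁ + 1/n₂) after 20% dropout; power = Φ(30/SE − 1.96).

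| Enrolled split | Evaluable | SE (m) | Power |
|---|---|---|---|
| 55:55 | 44:44 | 10.66 | 80.4% |
| 50:60 | 40:48 | 10.70 | 80.0% |
| 45:65 | 36:52 | 10.84 | 79.0% |

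**4. Cost of a site difference, over both sites.** There are 220 × 0.8 = 176 evaluable, 88 per arm. With no site difference, SE = 50√(2/88) = 7.54 m. With two equal sites and unadjusted, unrestricted allocation, the variance is multiplied by about 1 + (D/2)²/50².

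| Assumed D | Factor | SE (m) | Power for 30 m |
|---|---|---|---|
| 0 m | 1.00 | 7.54 | 97.8% |
| 20 m | 1.04 | 7.69 | 97.4% |
| 40 m | 1.16 | 8.12 | 95.9% |

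**5. What a site term alone recovers.** With unrestricted allocation and 88 evaluable per site, the expected value of n₁n₂/n at a site is (88 − 1)/4 = 21.75. The site-adjusted SE is then about 50/√(2 × 21.75) = 7.58 m, whatever D is. Stratified allocation gives about 7.54 m. The site term therefore recovers almost all of the loss, and stratification adds about 0.04 m.

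**6. Why the two belong together.** If allocation is stratified but the plain t-test is kept, its SD still contains the site difference. At D = 40 m that SD is √(50² + 20²) = 53.9 m, so the test reports an SE of about 8.12 m when the true one is 7.54 m.

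**The case against.** The strongest objection is that unrestricted randomisation is inferred from silence. The Randomization paragraph uses the plural for its random number sequences, which fits one list per site, and block details are often kept out of a protocol to protect concealment. This stands: every figure in step 2 is conditional on an unrestricted list. But the Allocation concealment paragraph speaks of one sequence in the singular, so the text leaves the method open. Whether allocation is stratified by site can be stated without disclosing block sizes.

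Three stronger readings are tempting, and the documents do not support them.
- A reader might infer that the sample size will be missed. The target is only approximate ("The number of participants to be enrolled in the study should be approximately 55 in each group"), so the 7.6% chance of an exact 55:55 split measures nothing that was promised, and step 3 shows that realistic splits hardly matter.
- A reader might infer that arm is confounded with site. Under 1:1 randomisation any imbalance is by chance; it adds noise, not systematic bias.
- A reader might infer that the harm is beyond repair once participants are allocated. That is true of the allocations but not of the lost precision, which a site term recovers (step 5). Analysis plans commonly settle such a term, and this trial's plan is not shown.

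Two further objections stand. The 40 m site difference exceeds the 30 m treatment effect and has no support in the protocol. Because the outcome is a change, a stable difference in how a site runs the test would largely cancel. And a site difference in the quality of yoga training would be a treatment-by-site interaction, which stratified allocation does not remove. Blocking also has a real cost in an open-label trial that uses envelopes, and unrestricted allocation of 220 people is a defensible choice. The early look is optional, and 8:19 is the edge of its range.

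**Conclusion.** The point holds as a minor, cheap improvement in precision. The protocol enrols 110 at each of two hospitals, states no site stratification or blocking, and specifies a between-group test without site. If the sequence is unrestricted, the split at a site may run from 45:65 to 65:45. The cost is 1.4 percentage points of power at single-site size for a 45:65 split. Over both sites it is about 0.4 points for an assumed 20 m site difference and about 2 points for 40 m; with no site difference it is close to nil. These figures rest on two equal sites, a within-site SD of 50 m, 20% dropout and a normal approximation. The stated 55 per group is correct on its own inputs, and no conclusion of the trial is put at risk.

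**What to change.** In the Randomization paragraph, state that allocation is stratified by study site using permuted blocks of randomly varying size, that block sizes are not disclosed to the sites, and that each site holds its own sequentially numbered opaque sealed envelopes. In Statistical methods, include site as a factor in the primary between-group comparison, for example a linear model with arm and site in place of the plain t-test.

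The cost is two blocked lists from the same independent statistician instead of one sequence. The required number of participants does not change and no staff are added. The downside is that allocations near the end of a block become somewhat easier to guess in an open-label trial; varying, undisclosed block sizes limit this. If a list per site or blocking is already in use, the only change to the Randomization paragraph is to say so.

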**Data management:**

**Statistical methods:**

The categorical variables in the study data will be summarized as number (percentage) and compared using chi-square test. The continuous data having normal distribution will be represented as mean (SD), and data not following normal distribution as median (min-max). Parametric data will be analyzed by paired t-test and independent sample t-test for within and between group analysis respectively whereas non-parametric data will be calculated by Wilcoxon signed rank test and Mann-Whitney test for within and between group analysis respectively. All the data analysis will be done using the STATA software version 16.1.

**Data Monitoring:** The study will be monitored by Data and Safety Monitoring Board (DSMB). An Interim analysis, if required can be done when at least 25% participants have completed their trial period.

**Ethics Approval:** The study protocol has been approved by the institutional Ethics committees of both the study sites viz., Government Medical College, Nagpur, India and Datta Meghe Institute of Medical Sciences, Wardha, India on 3^rd^ February 2021 and 24^th^ February 2021 (vide EC-CT-2019-0129 and EC/Pharmac/GMC/NGP/2309) respectively. The study will be conducted in accordance with the principles of Declaration of Helsinki and the ICMR’s National Ethical Guidelines for Biomedical and Health Research on Human Participants (2017).

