**Outcomes:**

Primary Outcome: Change in respiratory function to be assessed by San Diego shortness of breath Questionnaire, 6-minutes walk test and Pulmonary Function test.

Secondary Outcomes:

- Change in High-resolution Computed Tomography (HRCT) Chest
- Change in Fatigue score assessed by Modified Fatigue Impact Scale
- Change in Anxiety score assessed by Hospital Anxiety and Depression Scale Score
- Change in Sleep Quality assessed by Pittsburgh Sleep Quality Index
- Change in the quality of life assessed by COV19-QoL scale
- Safety of the interventions will be assessed by comparing hematological and biochemical investigations before and after the intervention period and Adverse Event/ Adverse drug reaction

**Timelines for Outcome assessment:** Subjective parameters and clinical assessment will be assessed at baseline, 15^th^ day, 30^th^ day, 60^th^ day and 90^th^ day. Laboratory parameters (CBC, LFT, KFT, HbA1c, Hs-CRP, D-dimer), Pulmonary function test and HRCT Chest will be done at baseline and after completion of study period i.e. 90^th^ day.

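### The between-group test of continuous outcomes is fixed without baseline adjustment; the planned test is valid, but ANCOVA on the baseline value would be more precise at almost no cost

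*Protocol*

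**What the plan says.** The Statistical methods section of the protocol assigns tests by distribution. For normal data: "Parametric data will be analyzed by paired t-test and independent sample t-test for within and between group analysis respectively". For other data: "non-parametric data will be calculated by Wilcoxon signed rank test and Mann-Whitney test for within and between group analysis respectively". No regression model, ANCOVA or covariate is named, and the section does not say which value (change or day 90) enters the between-group test.

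Two other sections point to change. Under Outcomes the primary outcome is "Change in respiratory function to be assessed by San Diego shortness of breath Questionnaire, 6-minutes walk test and Pulmonary Function test", and the five secondary efficacy outcomes are likewise defined as changes. Under Sample size the trial is planned "assuming improvement in 6-minutes walk test by 40 meter in Group I and a change of 10 meter in Group II". The SD there is 50 m, attributed to earlier studies.

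Baseline data will be available: "Subjective parameters and clinical assessment will be assessed at baseline, 15^th^ day, 30^th^ day, 60^th^ day and 90^th^ day". The same section has the pulmonary function test and HRCT done at baseline and at day 90.

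**The concern.** When an outcome is measured before and after treatment, the baseline value predicts the final value. A two-sample test of change uses baseline only by subtraction, which fixes its coefficient at 1. If the correlation rho between baseline and day 90 is below 1 and the SDs are equal, the best coefficient is rho. Subtraction then over-corrects: participants who start low tend to gain more, so an arm that starts lower by chance looks somewhat better.

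Two things follow. The interval around the treatment difference is wider than it need be, and the estimate keeps a residual dependence on chance baseline imbalance. ANCOVA estimates the coefficient from the data. Under randomisation it is, in large samples, never less precise than a test of change or of day-90 values.

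The protocol describes 1:1 random sequences and states no stratification on baseline function, so the design as written does not control such imbalance.

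**Working it through.** **Inputs from the protocol (Sample size):** difference 40 − 10 = 30 m; SD 50 m; "with 95% Confidence Level (α = 0.05) and 80% power"; 20% dropout; 55 per group and 110 at each of two sites.

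**Assumptions, not in the protocol:** the test is two-sided; 50 m is the SD of change; SDs are equal at baseline and day 90; rho is 0.3, 0.5, 0.7 or 0.9.

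**1. Reproduce the stated size.** n per group = 2 × (1.96 + 0.8416)² × 50² / 30² = 43.6, rounded up to 44. Allowing for dropout, 44 / 0.8 = 55. This matches the protocol and treats the 30 m as a difference between two changes.

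**2. Number evaluable.** Two sites of 110 give 220 enrolled, 110 per arm, and 110 × 0.8 = 88 evaluable per arm when pooled. The Dissemination section bars centres from reporting their data alone, so pooled figures come first. Figures for 44 per arm apply if each site's sample is analysed separately.

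**3. Variance ratio.** With a common SD σ, Var(change) = 2σ²(1 − rho) and the ANCOVA residual variance is σ²(1 − rho²). The ratio is (1 + rho)/2, so the residual SD is 50 × √((1 + rho)/2). The excess variance of the change-score test is 2/(1 + rho) − 1.

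| rho | ratio | residual SD | excess variance |
|---|---|---|---|
| 0.3 | 0.65 | 40.3 m | 54% |
| 0.5 | 0.75 | 43.3 m | 33% |
| 0.7 | 0.85 | 46.1 m | 18% |
| 0.9 | 0.95 | 48.7 m | 5% |

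**4. Precision and power.** Half-width = t × SD × √(2/n). For the change score with 88 per arm, SE = 50 × √(2/88) = 7.54 m, and 1.974 × 7.54 = 14.9 m. With 44 per arm, SE = 10.66 m, and 1.988 × 10.66 = 21.2 m. Power is from the noncentral t distribution at 30 m. One degree of freedom is deducted for the covariate.

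| Analysis | half-width, 88 per arm | power, 88 | half-width, 44 per arm | power, 44 |
|---|---|---|---|---|
| t-test on change | 14.9 m | 97.7% | 21.2 m | 79.5% |
| ANCOVA, rho 0.3 | 12.0 m | 99.8% | 17.1 m | 93% |
| ANCOVA, rho 0.5 | 12.9 m | 99.5% | 18.4 m | 89% |
| ANCOVA, rho 0.7 | 13.7 m | 99.0% | 19.5 m | 85% |
| ANCOVA, rho 0.9 | 14.5 m | 98.2% | 20.7 m | 81% |

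The narrowing is 1 − √((1 + rho)/2), which is 19%, 13%, 8% and 3% at either sample size.

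**5. Residual effect of imbalance.** A baseline difference of d moves the change-score estimate by −(1 − rho) × d. For d = 10 m the shift is −7, −5, −3 and −1 m at rho 0.3, 0.5, 0.7 and 0.9.

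This is the same loss as in step 4 seen from another side, not an additional one. At rho 0.5 with 44 per arm the implied baseline SD is 50/√(2 × 0.5) = 50 m. A 1-in-20 imbalance is 1.96 × 50 × √(2/44) = 20.9 m, which shifts the estimate by 10.4 m. That is close to √(21.2² − 18.4²) = 10.5 m, the part of the interval that ANCOVA removes.

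**The case against.** A reader might infer that the plan ignores the baseline and lets a chance imbalance pass straight into the efficacy estimate. The documents do not support that. The outcomes and the sample size are framed as changes, so baseline is already used by subtraction. An imbalance then enters only by the fraction 1 − rho and in the opposite direction. It would enter in the same direction, by rho, only if raw day-90 values were compared. The Statistical methods section does not rule that out, but nothing in the Outcomes or Sample size sections suggests it.

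A reader might also infer that the trial is underpowered for want of adjustment. With both sites pooled it is not: power for the 30 m difference is 97.7% without adjustment and gains at most about 2 points. The larger gains belong to 44 per arm.

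Further points on the other side are fair. The unadjusted test is valid, unbiased on average and consistent with the sample-size calculation. The study is labelled exploratory. The correlation is undocumented, and at 0.9 the gain is small. With the SD of change held at 50 m, a wide baseline spread implies a high correlation and therefore less to gain. The figures cover the 6-minute walk only; for other outcomes the size of the gain is unknown.

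It can also be said that covariate adjustment is usually left to a SAP, which may exist unseen. That carries less weight here. The protocol does not leave the test open but names it, and its Protocol Amendments section treats changes to the method of analysis as amendments to be reported.

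**Conclusion.** The point holds as one of efficiency, not of validity. The protocol fixes an unadjusted between-group test although a baseline will be available for its change outcomes, and it does not say which value is tested. On the natural reading (change), the planned analysis is sound but less precise than ANCOVA and leaves a residual effect of baseline imbalance, which its confidence interval already covers.

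For the pooled 6-minute walk comparison the benefit is a 95% CI narrower by 19%, 13%, 8% or 3% at correlations of 0.3, 0.5, 0.7 or 0.9, with little change in power. If only 44 per arm were analysed, the power gain would be about 2 to 14 points over the same range. All of this rests on 50 m being the SD of change, equal SDs at the two times, and an assumed correlation. The change is worth making because it costs almost nothing.

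**What to change.** In Statistical methods, make the between-group analysis of continuous outcomes an ANCOVA: day-90 value as response, study arm as factor, and the baseline value of the same measure as covariate. Report the adjusted mean difference with its 95% CI. For clearly non-normal outcomes, use a rank-based ANCOVA or an ANCOVA on transformed values. Keep the t-test or Mann-Whitney test as a supportive analysis, and state that it compares change from baseline.

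Baseline alone is enough. Time since the positive test is not a good second covariate, because the Eligibility Criteria accept either RT-PCR or IgM positivity and the interval does not measure the same thing in everyone.

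Cost: one amended sentence and one degree of freedom. No new data, visits or participants are needed.
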